# Evaluation of the Teaching Recovery Techniques community-based intervention for unaccompanied refugee youth experiencing post-traumatic stress symptoms (Swedish UnaccomPanied yOuth Refugee Trial; SUPpORT): study protocol for a randomised controlled trial

**DOI:** 10.1186/s13063-019-3814-5

**Published:** 2020-01-10

**Keywords:** Teaching Recovery Techniques, Post-traumatic stress disorder, Unaccompanied refugee minors, Randomised controlled trial

## Abstract

**Background:**

In 2015, 162,877 persons sought asylum in Sweden, 35,369 of whom were unaccompanied refugee minors (URMs). Refugee children, especially URMs, have often experienced traumas and are at significant risk of developing mental health problems, such as symptoms of post-traumatic stress disorder (PTSD), depression and anxiety, which can continue years after resettlement. The Swedish UnaccomPanied yOuth Refugee Trial (SUPpORT) aims to evaluate a community-based intervention, called Teaching Recovery Techniques (TRT), for refugee youth experiencing PTSD symptoms.

**Methods/design:**

A randomised controlled trial will be conducted in which participants will be randomly allocated to one of two possible arms: the intervention arm (*n* = 109) will be offered the TRT programme, and the waitlist-control arm (*n* = 109) will receive services as usual, followed by the TRT programme around 20 weeks later. Outcome data will be collected at three points: pre-intervention (T1), post-intervention (T2; about 8 weeks after randomisation) and follow-up (T3; about 20 weeks after randomisation).

**Discussion:**

This study will provide knowledge about the effect and efficiency of a group intervention for URMs reporting symptoms of PTSD in Sweden.

**Trial registration:**

ISRCTN, ISRCTN47820795. Prospectively registered on 20 December 2018.

## Background

In 2015, 162,877 persons sought asylum in Sweden, 35,369 of whom were unaccompanied refugee minors (URMs) [40]. Most URMs (86%) were boys, mainly from Afghanistan, Syria, Somalia and Eritrea. The number of new applications has dropped sharply since 2015; however, Sweden is still one of the main destinations for URMs, and many of the minors who arrived in 2015 still remain in the country. Apart from adverse events before and during migration, the asylum and resettlement process per se involves stressors, such as lack of control and insecurity while waiting for a decision of the asylum application. Both pre- and post-migration factors severely increase the risk of developing mental health problems [32].

Vulnerability is experienced by many immigrants and refugees, yet URMs appear to be the most vulnerable [4]. A study on 307 URMs in Norway showed that 54% reported high levels of post-traumatic stress disorder (PTSD) symptoms [14]. A study of 206 (mainly male Afghani) URMs in Sweden reported that 76% screened positive for PTSD symptoms [27]. Another Swedish study of 42 children from refugee families indicated that 21% met the full criteria for PTSD, and a further 31% suffered from severe PTSD symptoms [1]. The prevalence of PTSD did not decrease at the 2.5-year follow-up [1]. Longitudinal studies of URMs confirm high levels of mental health problems several years after resettlement [20, 43]. Thus, PTSD symptoms are not only prevalent in asylum-seeking children and youth, they also tend to persist [41]. Considering the associations between PTSD and lower academic achievements [44] and unemployment [45], integration might also be aggravated.

There is general agreement in the literature that trauma-focused cognitive behavioural therapy (TF-CBT) is the method of choice for treating PTSD and other internalising and externalising symptoms in trauma-exposed children and youth [15]. In Sweden, although it is the treatment of choice, TF-CBT is unfortunately not equally accessible or available in a timely manner for refugee children and youth due to resource constraints within specialised services. PTSD is associated with other mental health disorders such as anxiety, depression and substance use and, when untreated, it can lead to functional impairment in school and work, as well as increase the risk of suicide. For such a large group within society to experience mental health problems and associated poor health and integration outcomes without receiving the necessary support is unacceptable. There is a need to develop a stepped-care model with light-touch interventions tied into specialised services.

## Teaching Recovery Techniques

The Children and War Foundation, based in the UK and Norway, utilised TF-CBT techniques to develop Teaching Recovery Techniques (TRT) [34, 46]. The brief manualised intervention aims to increase coping and promote recovery from PTSD in children aged eight and above in conflict/disaster. It was specifically designed to meet the needs of low-resource settings, where a lot of children require intervention. High acceptability and large effect sizes for decrease in symptoms of both PTSD and depression have been reported in studies from Gaza [3, 25] and after the tsunami in Thailand [23].

In Sweden, an exploratory trial of TRT with 46 URM youth (mainly male, aged 13–18 years) yielded promising results, with significant decreases in both PTSD and depression reported [28]. More than a fifth of participants recovered from their PTSD symptoms, while a third recovered from depressive symptoms [28].

The Swedish UnaccomPanied yOuth Refugee Trial (SUPpORT) aims to further strengthen the evidence base of TRT among refugee youth (aged 14–20 years for the present project) residing in Sweden. By applying a randomised controlled approach, outcomes can be attributed to the TRT intervention. The present paper outlines the protocol for SUPpORT.

## Objectives

The objectives of the trial are:
To evaluate whether the TRT programme has a positive effect on unaccompanied refugee youth mental health in comparison to similar youth who only receive services as usualTo evaluate whether the TRT programme has a positive effect on unaccompanied refugee youth self-efficacy and well-being, which relate to the programme theory of changeTo identify which subgroups report the most/least benefit of TRTTo describe the extent to which TRT is implemented with fidelity to programme designTo estimate the cost-utility and cost-effectiveness of the TRT programme.

It is hypothesised that, when compared with youth who have not received the intervention (the waitlist-control arm), youth who have received TRT (the intervention arm) will demonstrate fewer self-reported symptoms of mental ill health, specifically PTSD, depression and anxiety symptoms. It is further hypothesised that, when compared with the waitlist-control arm, the intervention arm will report greater self-efficacy and well-being.

## Methods

### Design

A two-arm randomised waitlist-control superiority trial (1:1 allocation ratio) will be conducted to evaluate the effectiveness of the TRT programme in improving mental health outcomes in unaccompanied refugee youth who have self-reported symptoms of PTSD. The intervention arm will be offered the TRT programme immediately after randomisation and the waitlist-control arm around 20 weeks later; both trial arms will have access to services as usual. Assessments will take place at three points: pre-intervention (T1), post-intervention (T2; about 8 weeks after randomisation) and follow-up (T3; about 20 weeks after randomisation). See Fig. 1 for an overview of assessments. The Standard Protocol Items: Recommendations for Interventional Trials (SPIRIT) checklist is presented in Additional file 1.

**Fig. 1 Fig1:**
[figure not shown]
SUPpORT schedule of enrolment, interventions and assessments

### Setting

TRT-trained ‘group leaders’ will deliver the intervention, with two group leaders for each group (with the assistance of interpreters, if necessary). The interventions will be delivered in a range of community settings (e.g. health care centres, social service group homes, non-governmental organisations [NGOs]) across Sweden. Sites include both urban and rural municipalities that have accepted to host refugees. To promote intervention stability, it is recommended that each site has an assigned local coordinator and at least one experienced group leader (i.e. one who has conducted at least two previous TRT groups). Supervision will also be offered to TRT group leaders. Assessments for the randomised controlled trial (RCT) will also take place in community settings.

### Participants

Youth are eligible to participate if all of the following criteria are satisfied at the time of randomisation:
The youth is aged 14 to 20 years old.The youth has spent 5 years or less in Sweden.The youth arrived in Sweden unaccompanied.The youth screens positive on the Children’s Revised Impact of Event Scale (CRIES-8) PTSD screening tool (≥ 17 points).The youth is interested in participating in a group intervention.The youth consents to be randomised.The legal guardian consents to participation if the youth is < 15 years old.Caregiver contact details are provided if the youth is < 18 years old.There is no ongoing treatment where a therapist advises against participation in TRT.

### Recruitment

Youth (males and females) will be referred to the trial by community workers (e.g. nurses, social workers, NGO staff members) who have concerns about the youth’s mental health. Youth can also self-refer. The CRIES-8 [21] will be used to identify youth with symptoms of PTSD. Those with scores ≥17 will be offered participation in the study. The Child Health and Parenting (CHAP) research group at Uppsala University has established relationships with community sites with TRT-trained staff across Sweden (e.g. Huddinge, Linköping, Uppsala, Östersund, Stockholm, Västerås). New sites will be approached during the trial period. It is anticipated that around 10 sites will recruit to the trial. Information about the study will be distributed to community sites directly by CHAP and posted online on the CHAP website. In an exploratory study, 90% of those screened for participation met the cutoff on the CRIES-8 [28]. The treatment retention rate was 59%, with most dropouts occurring right before or just after the start of the group. To take these factors into account, an over-recruitment is planned for the present project.

Youth who meet the inclusion criteria will be invited to a group ‘information and assessment’ meeting. Written informed consent and pre-intervention measures will be collected by the research team at the meeting prior to randomisation on site. The informed consent relates only to the SUPpORT study; no ancillary studies are planned. No biological specimens will be collected as part of the SUPpORT study.

If a youth is randomised to the intervention group but does not attend the TRT sessions, he/she will remain in the research study and will be contacted at the data collection points. The youth (and legal guardian if the youth is < 15 years) will be informed of his/her right to withdraw from the research study. Youth will be informed that they can withdraw at any time and do not need to give a reason, and there will be no negative outcomes from withdrawing. No further data will be collected for withdrawn cases. All existing data will be retained unless a youth/legal guardian also asks for it to be removed (youth/legal guardians will be informed that this is possible up to the point that the data is analysed). Youth will be able to receive the TRT programme regardless of whether they withdraw their involvement in the research study.

In order to minimise attrition, the trial has been branded as the SUPpORT project (Swedish UnaccomPanied yOuth Refugee Trial); participants will be made aware of what involvement in the project entails from the outset; youth will be offered an incentive (shopping vouchers valued at 100SEK) at each data collection session to compensate for their time; and the research team will work to keep community contacts involved in the trial and help them to make referrals.

### Sample size

Recruitment of 218 eligible youth to the project (109 per trial arm) will allow detection of an effect size of 0.5 at *p* < 0.05 with 80% power and allows for a study dropout rate of up to 41%, as informed by an exploratory study (an effect size of 0.5 requires a minimum sample size of 64 participants per trial arm).

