### Intervention arm

The intervention arm will receive the Swedish translation of the TRT programme and may access services as usual. The intervention uses TF-CBT as its foundation, agreed to be the method of choice for treating PTSD in children and adolescents [15]. The group-based cognitive behavioural programme includes five youth sessions and two caregiver sessions. A ‘getting to know each other session’ will be offered prior to the core TRT sessions and a ‘follow-up session’, which consolidates learning and enables participants to talk about their experience of taking part in the programme, will be offered afterwards. Sessions will be delivered over 7 consecutive weeks. Each session will last 2 h (including a break). For unaccompanied refugee youth, the ‘caregiver’ is a nominated adult (e.g. their legal guardian, an adult from their family home or a school counsellor). The sessions for youth incorporate several components of TF-CBT, including psychoeducation, affective modulation skills, cognitive coping and processing, trauma narrative, overcoming trauma reminders and future development. The caregiver sessions include an introduction to the TRT method and an overview of the content in the youth sessions. The caregivers are instructed in how to support the youth through listening and comforting, when needed, as well as through maintaining routines and activities. Additionally, the caregivers receive information on how to seek care if the youth needs additional help after TRT. Caregiver sessions are delivered without the youth, in parallel with the first two youth sessions. TRT group leaders receive 3 days of training in programme delivery from BRIS (Children’s Rights in Society). Two group leaders deliver each group (with the assistance of an interpreter, if necessary).

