### Statistical methods

Baseline and demographic characteristics will be summarised using means and standard deviations (or medians and interquartile ranges) for continuous variables and percentages for categorical variables. A set of strategies will be employed to minimise the amount of missing data (e.g. offering incentives for completing follow-ups). Reasons for dropouts for each condition will be reported. The possible impact of missing data will be examined via sensitivity analyses of augmented data sets. Including the dropouts and participants with missing data will be made possible by using modern analytical methods.

The comparison of the trial arms will use an intention-to-treat framework with participants analysed according to the trial arm to which they were randomised, regardless of whether or not they received the intervention. Linear mixed models will be used to compare outcomes for the trial arms. The primary outcome is total score group differences on the mental health outcome measures (i.e. CRIES-13, PHQ-9, GAD-7) after programme delivery (T2). The secondary outcomes are mental health outcome measures (i.e. CRIES-13, PHQ-9, GAD-7) total scores at endpoint (T3) and GSE and Cantril Ladder total scores after programme delivery and at endpoint (T2 and T3).

For the mental health outcome measures (CRIES-13, PHQ-9,; GAD-7), participants will also be classified as ‘recovered’, ‘improved’, ‘unchanged’ or ‘deteriorated’ based on the Reliable Change Index (RCI) and Clinically Significant Change (CSC) approach [10, 13]. This approach incorporates both a measure of whether the change in scores is larger than what is expected due to outcome measure reliability as well as the participant’s shift from a clinical state to a non-clinical state. The proportions of classifications will be compared across the trial arms.

Fidelity to the design of the intervention will be summarised using descriptive statistics. It will be assessed in terms of the different dimensions measured (adherence and dose). A secondary analysis will be undertaken to quantify the extent to which the intervention effect on the primary outcomes is determined by participation in the intervention (number of sessions received). Further moderation analyses will examine the associations between improvement status and participants’ characteristics (e.g. age, gender, suicidal ideation).

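### The sample size treats all youth as independent although TRT is delivered in groups in one arm, so the claim of 80% power at up to 41% dropout has no margin for within-group correlation

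*Protocol article*

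**What the plan says.** Under Sample size, the protocol says that 218 youth, 109 per arm, "will allow detection of an effect size of 0.5" "at *p* < 0.05 with 80% power" and that this tolerates dropout of up to 41%. The basis is that "an effect size of 0.5 requires a minimum sample size of 64 participants per trial arm". No group size, ICC or design effect is given.

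Youth are randomised individually, 1:1 (Randomisation). On delivery, the Intervention arm section says: "The group-based cognitive behavioural programme includes five youth sessions and two caregiver sessions". The Setting section describes delivery "with two group leaders for each group (with the assistance of interpreters, if necessary"). The waitlist arm has services as usual until about week 20 (Design; Control arm), so it has no TRT groups at T2, the primary time point, or before T3.

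On analysis, Statistical methods says: "Linear mixed models will be used to compare outcomes for the trial arms". No random effects are named, so a term for TRT group is neither planned nor excluded there.

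**The concern.** Youth in the same TRT group share two leaders, sometimes an interpreter, and each other's company for seven weeks before T2. Their scores may therefore be more alike than those of youth in different groups. Individual randomisation does not remove this, because the correlation arises after allocation. It affects the intervention arm only and raises the variance of that arm's mean.

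Two things follow. The sample size, if computed as though all youth were independent, overstates the power of a correct analysis. And if the analysis itself left out the group level, the standard error of the arm difference would be too small and the test would reject too often. The first follows from what the Sample size section states. The second depends on a model structure that the protocol does not give.

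**Working it through.** **1. Reproducing the plan's figure.** Inputs from Sample size: standardised difference 0.5, alpha 0.05 (taken as two-sided; one-sided would give 50 per arm), power 80%. The two-sample t-test needs 63.77 per arm, so 64, and power at 64 is 80.1%. Inflating for loss: 64 / (1 − 0.41) = 108.5, so 109 per arm and 218 in total. Both figures match, so the design effect is 1 and no clustering allowance is hidden in them.

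**2. Margin.** At the stated loss, 109 × 0.59 = 64.3 remain against 63.77 needed. With a design effect DE in one arm, the required number per arm scales as 63.77 × (DE + 1)/2. Setting this equal to 64 gives DE = 2 × 64/63.77 − 1 = 1.007. With 6 analysed per group that is an ICC of 0.007/5, about 0.0015. The normal formula, which needs slightly fewer youth, gives an ICC of about 0.008. On either basis the margin is negligible.

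**3. Power with grouping.** Group size and ICC are assumptions: 4 to 10 youth allocated per group, ICC 0.01 to 0.10. If 41% are lost, the analysed group size m is 0.59 times the allocated size, so 2.4 to 5.9. With n = 64 analysed per arm and unit variance:

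- DE = 1 + (m − 1) × ICC, intervention arm only
- SE = sqrt(DE/n + 1/n)
- number of groups k = n/m
- Satterthwaite df = (DE/n + 1/n)² / [(DE/n)²/(k − 1) + (1/n)²/(n − 1)]
- power from the noncentral t with noncentrality 0.5/SE

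Example, 6 allocated per group and ICC 0.05: m = 3.54; DE = 1 + 2.54 × 0.05 = 1.127; SE = sqrt(2.127/64) = 0.182; k = 18.1; df = 50; noncentrality 2.74; power 77%.

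Power at 64 analysed per arm:

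| Allocated per group (analysed) | ICC 0.01 | ICC 0.05 | ICC 0.10 |
|---|---|---|---|
| 4 (2.4) | 79% | 78% | 77% |
| 6 (3.5) | 79% | 77% | 74% |
| 8 (4.7) | 78% | 75% | 71% |
| 10 (5.9) | 77% | 73% | 68% |

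If 6 is instead the analysed size (about 10 allocated), DE = 1 + 5 × 0.05 = 1.25 and power at ICC 0.05 is 73%. The normal approximation, which ignores the limited degrees of freedom that few groups supply, gives 76% for the same case.

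**4. Dropout at which 80% is kept.** For ICC 0.05 and 6 analysed per group, n = 75 gives SE = sqrt(2.25/75) = 0.173, df = 34 and power 80%. That is a loss of 1 − 75/109 = 31%. With all 109 per arm analysed, power is 93%.

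**5. Type I error if the group term were left out.** The rate is 2 × [1 − Φ(1.96/sqrt((DE + 1)/2))]. For 6 allocated and ICC 0.05, DE = 1.127 gives 5.7%. For 10 allocated and ICC 0.10, DE = 1.49 gives 7.9%. Over the whole grid in step 3 the rate is about 5% to 8%.

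**The case against.** The strongest reply has four parts.

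- **The inputs are assumed.** The protocol gives neither ICC nor group size. At ICC 0.01 power is 77% to 79%, within about three points of the target. This stands, and it is why the result is a range.
- **The full 41% loss may not occur.** The figure comes from treatment retention of 59% in the exploratory study (Recruitment). In this trial non-attenders stay in the study and are contacted for assessment, and there are retention measures. Most dropouts in the exploratory study left around the start of the group, so many assessed youth might share little group exposure, which would tend to lower the ICC. Baseline adjustment could also recover power. None of this is quantified in the document. It stands as a reason why achieved power may be adequate, but it does not rescue the claim as written, which is made at 41%.
- **The random-effects structure may be in an analysis plan that is not shown.** This stands. A reader might infer that the test will ignore grouping and be anti-conservative. The protocol does not support that: it plans linear mixed models and does not rule out a group term.
- **Severe figures can be produced by mixing inputs.** Pairing 64 analysed per arm with 8 to 10 analysed youth per group and ICC 0.10 gives power of 58% to 63% and type I error of 9% to 10%. After 41% loss, those group sizes imply about 14 to 17 allocated per group (8/0.59 and 10/0.59). Nothing in the document suggests groups of that size, so these figures should not be relied on.

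**Conclusion.** The Sample size section makes no allowance for clustering by TRT group in the intervention arm. Its two claims, 80% power and tolerance of 41% dropout, hold together only if within-group correlation is essentially zero. The shortfall is small to moderate: power of about 68% to 79% at 64 analysed per arm, with 77% as a central case (ICC 0.05, 6 allocated per group). These values rest on the assumed group sizes and ICCs, on the full 41% loss and on an analysis without gain from baseline adjustment.

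A reader might conclude that the trial is underpowered outright. The document does not support that, because 80% is still reached when loss is lower, for instance at about 31% with ICC 0.05 and 6 analysed per group. The type I error of about 5% to 8% is conditional on a group term being omitted, which the protocol does not say.

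**What to change.** - **Sample size section:** state an assumed ICC and analysed group size, and give either the power at 41% loss or the dropout rate at which 80% power is kept. Say whether the group size is before or after loss, since at ICC 0.05 a group of 6 gives 77% on one reading and 73% on the other.
- **Primary analysis:** state in the protocol, or confirm in the analysis plan, that the linear mixed model has a random effect for assigned TRT group in the intervention arm only, with small-sample degrees of freedom (Satterthwaite or Kenward-Roger).
- **Data:** record the allocated TRT group for every intervention-arm youth, including those who never attend. The Intervention fidelity section provides for attendance lists but does not say that these show allocated group.

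The cost is a slightly lower stated power, one more variance term and one recorded variable. No extra participants are required.
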